### Sampling Plan

#### Hypothesis 1

Sample size calculation for quality of life measured by the EQ-HWB-9 using repeated measures linear mixed modeling assumes three groups will be assessed with (1) low, (2) medium, and (3) high regular meditation dosage. Given the limited research on the effects of long-term regular meditation practice, calculating power is challenging. We have therefore used conservative power calculations that may err on the side of underestimating the power of our primary analysis but allow for use of the effect information and analytic tools that are available. We have conducted power analysis using 3 levels of variation in the predictor of monthly meditation amount, rather than the continuous variable we plan to use in our final analysis. This is to allow for the use of an analytic power calculation method for our repeated measures design, rather than simulation measures, which would be highly speculative with the limited real and independent data available for our outcome measure [64]. Ten measurement time points were also used, rather than the 12 that will be included in our analysis, as this is the maximum for GLIMMPSE (University of Florida and University of Colorado Denver) power analysis software [65].

Sample size calculation for quality of life measured by the EQ-HWB-9 using repeated measures linear mixed modeling assumes three groups will be assessed with (1) low, (2) medium, and (3) high regular meditation dosage. No increase in EQ-HWB-9 scores was predicted for the low meditation group [58]. For the high meditation group, we estimate a stepwise increase to a minimum of a 2.25-point EQ-HWB-9 increase (out of a possible 9‐45 points) from baseline to time point 5, corresponding to the change in EQ-HWB-9 from baseline to 6 months associated with improvement in mental health in a validation of the EQ-HWB-9 sensitivity to change [59]. We then predict a further 2.25-point increase to time point 10, for a total increase of 4.5 points. For the moderate meditation group, stepwise improvement was predicted with a minimum of a 2.25-point EQ-HWB-9 increase from baseline to time point 10. Baseline EQ-HWB-9 is set at 19.6, with an SD of 7.0, as per our nationally representative surveys [66]. Using GLIMMPSE [65] with 95% power and 0.05 2-tailed type 1 error rate, sample size was calculated at 435 participants. We estimated a 20% loss to follow-up over one year, bringing the sample size required to 522 participants.

#### Hypothesis 2

There is limited research available on the effects of long-term meditation on mental well-being using the 7-item SWEMWBS. However, there is published data available for the 14-item version (Warwick-Edinburgh Mental Well-being Scale; WEMWBS) for postinitial meditation instruction [22] and at one year follow-up [23]. These 2 mental well-being scales are highly correlated (0.954) [61], so we have used the data available for the WEMWBS in our power calculation.

Sample size analysis for the effect of meditation practice amount on mental well-being (WEMWBS) using repeated measures linear mixed modeling assumes three groups will be assessed with (1) low, (2) medium, and (3) high meditation dosages, with 10 measurement time points, as required for the use of GLIMMPSE [65] as an analytic power calculation method outlined above. The baseline mean WEMWBS is set at 49.61, the postintervention level found for the introductory meditation arm, and the SD of 8.88 [22] for all groups and time points. No increase in WEMWBS scores [62] is predicted for the low meditation group. For the moderate meditation group, we predict stepwise improvement of 3 points to a final time point mean of 51.06 (SD 8.88), corresponding to a one-year follow-up of an MBP, regardless of regular meditation rates after course completion [23]. For the high meditation group, we estimate stepwise improvement to an 8-point increase from baseline to final time point (mean 57.61, SD 8.88), representing a minimum individual detectable change that has been reported for the WEMWBS [63]. Using GLIMMPSE [65] with 95% power and 0.05 2-tailed type 1 error rate, the required sample size to detect these effects was 201 participants, 242 assuming a 20% loss to follow-up.

#### Hypotheses 3 and 4

There is limited research investigating whether meditation practice being spiritual or secular moderates the effect of practice time. Previous studies have shown evidence that engaging in regular spiritual mind-body practices may moderate the effect of an initial meditation program at 6 months, such that stress and depressive symptoms are only improved compared to treatment as usual for those individuals who do not regularly engage in spiritual mind-body practices [67]. However, this was not compared to similar secular meditation practices. Our prospective longitudinal study found that those with a spiritual goal for meditation practice obtained less benefit from their meditation practice for life satisfaction and positive affect [32]. Nevertheless, to our knowledge, the moderating effect of practicing within a spiritual tradition on quality of life or well-being as outcomes is yet to be investigated or observed over a one-year follow-up. Therefore, potential effect sizes for these analyses are highly uncertain. As such, to account for testing these hypotheses, we plan to increase our sample by an additional 20% from what is required for power to test our primary outcome (Hypothesis 1) to 627 participants. With this sample and our planned model, setting power to 0.95 and significance to 0.05 2-tailed, we will be powered to detect a moderation effect of f^2^=0.0352 [68].

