**Methods:**

We will conduct a prospective longitudinal cohort study of 600 beginner meditators in Australia, New Zealand, the United States, and the United Kingdom over a 1-year period. Meditation practice frequency and duration will be reported weekly through the ambulatory assessment app Fabla (Emory University), with sampling of the primary outcome of quality of life and secondary outcome of mental well-being at monthly intervals. Practice characteristics, including secular versus spiritual practice, will also be reported monthly, as will the costs of meditation and mental health care and the incidence, severity, and duration of any adverse effects. Potential confounders, including baseline mental health symptoms, social support, and sociodemographics, will be controlled for in linear mixed models. An incremental cost-effectiveness ratio will be calculated, and sensitivity analyses will be conducted.

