Finally, the study aims to document the incidence and impact on daily function of any challenging, difficult, or distressing meditation-related experiences (Aim 6). Meditation-related adverse effects (MRAEs) will be defined as any challenging, difficult, or distressing meditation-related experiences that impact everyday functioning. Our aims, hypotheses, and possible interpretations are summarized in Table 1 below.

**Table 1. T1:** Protocol Design table.

Question	Hypothesis	Sampling plan (eg, power analysis)	Analysis plan	Interpretation given to different outcomes
Does regular meditation practice after initial instruction increase quality of life?	The amount of meditation practice during approximately the first year predicts practitioners’ quality of life, such that a greater amount leads to greater quality of life.	A total number of 522 gives 95% power to detect the variance in quality of life (EQ-HWB-9^a^) explained by monthly meditation practice observed in linear mixed model analysis, at a 2-tailed significance level of 0.05, accounting for an estimated 20% loss to follow-up.	Linear mixed model of the fixed effect of the amount of meditation in the past month on quality of life in the past week (EQ-HWB-9), controlling for the confounding factors of age, caring status, education, mental health diagnosis, commitment to meditation, and membership of a practice support community at baseline.	A positive/negative and statistically significant association between the amount of meditation in the past month on quality of life and in the past week will suggest that regular meditation practice after initial instruction increases/decreases quality of life in a linear fashion. A nonsignificant association will suggest an absence of evidence for either of these effects.

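### The 20% loss to follow-up is applied as ×1.2 instead of ÷0.8, so 522 and 242 fall slightly short of their stated 95% power; separately, the Hypothesis 2 moderate-group gain and final mean disagree

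*Protocol article*

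**What the plan says.** **Hypothesis 1 (Sampling Plan).** The calculation is made "Using GLIMMPSE [65] with 95% power and 0.05 2-tailed type 1 error rate", and the "sample size was calculated at 435 participants". Attrition follows: "We estimated a 20% loss to follow-up over one year, bringing the sample size required to 522 participants". Table 1 repeats this as a power claim that already allows for the loss: "A total number of 522 gives 95% power".

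**Hypothesis 2 (Sampling Plan).** The result is that "the required sample size to detect these effects was 201 participants, 242 assuming a 20% loss to follow-up". Table 1 again attaches 95% power to 242 with the loss allowed for. The baseline mean is 49.61 in all groups. For the moderate group, "we predict stepwise improvement of 3 points to a final time point mean of 51.06 (SD 8.88"). The high group gains 8 points, to 57.61.

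**Hypotheses 3 and 4.** The plan is to "increase our sample by an additional 20% from what is required for power to test our primary outcome (Hypothesis 1) to 627 participants". Table 1 gives 627 for Hypothesis 3 and 291 for Hypothesis 4, each as the preceding requirement plus 20%.

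**Cohort size.** The abstract describes a "prospective longitudinal cohort study of 600 beginner meditators".

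**The concern.** Multiplying by 1.2 is not the inverse of losing 20%. If a fraction d is lost, n/(1 − d) must be enrolled to keep n. The stated totals therefore do not deliver the number of completers that the same section says is needed, and Table 1's power statements are wrong as written. The moderation totals are built on those figures, so their advertised 20% margin is smaller than it looks. The reader is also left with two cohort sizes, 600 and 627, while recruitment is still open (341 baselines by May 14, 2026).

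The second matter is independent. The stated gain and the stated final mean of the Hypothesis 2 moderate group cannot both be right, so the text does not show which input produced 201.

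**Working it through.** **1. Reproducing the plan's figures (multiply by 1.2)**

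| Hypothesis | Calculation | Stated |
|---|---|---|
| 1 | 435 × 1.2 = 522 | 522 |
| 2 | 201 × 1.2 = 241.2 → 242 | 242 |
| 3 | 522 × 1.2 = 626.4 → 627 | 627 |
| 4 | 242 × 1.2 = 290.4 → 291 | 291 |

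All four match, which identifies the rule that was used.

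**2. What remains after a 20% loss**

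- 522 × 0.8 = 417.6, against 435 required.
- 242 × 0.8 = 193.6, against 201 required.
- Loss actually covered: 1 − 435/522 = 16.7%, and 1 − 201/242 = 16.9%.

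**3. Figures that cover a 20% loss**

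- Hypothesis 1: 435/0.8 = 543.75 → 544.
- Hypothesis 2: 201/0.8 = 251.25 → 252.
- Hypothesis 3, same 20% allowance: 544 × 1.2 = 652.8 → 653.
- Hypothesis 4, same 20% allowance: 252 × 1.2 = 302.4 → 303.
- Margins over 544: 627/544 = 1.153 and 600/544 = 1.103.

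**4. Power at the retained numbers**

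The noncentrality is set so that the required n gives exactly 95% at two-sided 0.05, then scaled by retained n over required n. With one degree of freedom:

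- (1.960 + 1.645)² = 12.995 at 435.
- At 417 the value is 12.995 × 417/435 = 12.457. Its square root is 3.529, and 3.529 − 1.960 = 1.569, which is 94.2% power.

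The article does not give the test's degrees of freedom, so a noncentral F was run with numerator df from 1 to 18. Lost participants are counted as contributing nothing.

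| Retained | Required | Power |
|---|---|---|
| 417 (522 enrolled) | 435 | 93.9–94.2% |
| 193 (242 enrolled) | 201 | 93.9–94.2% |
| 480 (600 enrolled) | 435 | 96.6–97.1% |

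627 enrolled retains 627 × 0.8 = 501.6, also above 435.

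**5. The Hypothesis 2 moderate group**

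- 49.61 + 3 = 52.61, not 51.06.
- 51.06 − 49.61 = 1.45, not 3.
- High group as a control: 49.61 + 8 = 57.61, as stated. Gains are therefore measured from 49.61, and the moderate-group line is inconsistent.

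**6. Which value produced 201?**

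The article states neither the correlation between time points nor the exact test. Assumed here: three equal groups, 10 time points, a group-by-time Hotelling-Lawley test, and compound symmetry.

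| Correlation | H1 | H2, final mean 51.06 | H2, final mean 52.61 |
|---|---|---|---|
| 0 | 432–435 | 201 | 222 |
| 0.1 | 390–393 | 180 | 201 |

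The H1 range is for a straight-line rise and for one with half the gain reached by time point 5. At zero correlation both 435 and 201 are reproduced, the latter with 51.06. A 3-point gain also gives 201 at correlation 0.1, but Hypothesis 1 would then need about 390. This favours 51.06 as the value entered, as an inference and not a demonstration.

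**The case against.** The strongest reply is that nothing practical turns on this. No one plans to stop at 522 or 242; the cohort is 600 or 627, and either leaves more than 435 after a 20% loss. The planned analysis is a REML mixed model on monthly outcomes, so a participant lost in month eight still contributes earlier months. The article also calls its power calculation conservative, because it uses three dose levels in place of a continuous predictor and 10 time points in place of 12.

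Most of that stands. It makes about 94% a lower bound and removes any case for more recruitment. It does not make ×1.2 the right inflation for a 20% loss, and the stated conservatism concerns dose levels and time points, not attrition.

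Four stronger readings are tempting, and the document does not support them:

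- **The moderate-group mean undermines every total.** It enters only Hypothesis 2 and so bears on 201, 242 and 291. It has no part in 522 or 627.
- **The step to 627 is itself an error.** An additional 20% on 522 is properly ×1.2. The 627 is off only because its base is. The 20% is also an allowance made because moderation effect sizes are uncertain, so a 15% margin breaks no derived requirement.
- **There are four competing cohort targets.** 522 and 242 are minimums for single hypotheses. Only 600 and 627 compete.
- **201 is wrong.** That depends on what was entered in the software, which the article does not say.

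**Conclusion.** The attrition error is certain and rests on the article's own numbers: 522 and 242 cover a loss of about 17%, not 20%. Table 1's claim of 95% power after the loss is overstated by about one percentage point, on the assumption that dropouts contribute no data. The true shortfall under the mixed model would be smaller.

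The margin for the moderation hypotheses is about 15% at 627 and about 10% at 600, where 20% is stated. The cohort size is given two ways.

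The Hypothesis 2 contradiction (3 points against 1.45) is also certain. Its consequence for 201 is not: the number stands if the value entered was the intended one, and otherwise becomes about 222 under an assumed zero correlation.

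A reader might infer that the study is underpowered or must recruit more. It need not: 600 enrolled retains 480, with about 97% power for Hypothesis 1 on the plan's assumptions, and 480 is well above 201 or 222 for Hypothesis 2. These are stated figures to correct before publication of results, not a defect in the design.

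**What to change.** 1. **Hypothesis 1:** in the Sampling Plan and Table 1, restate 522 as 544, or keep 522 and say it gives about 94% power after a 20% loss.
2. **Cohort target:** give one figure, 600 or 627, in the abstract, Sampling Plan and Table 1, with its true margin over 544 (about 10% or 15%).
3. **Hypothesis 2:** state which moderate-group final mean was entered in the software.
   - If 51.06 was entered and intended, correct the gain to 1.45 points, keep 201, and restate 242 as 252 and 291 as 303.
   - If 52.61 (a 3-point gain) was entered, correct the printed mean, keep 201, and use the same restated totals.
   - If 51.06 was entered but 3 points was intended, rerun. As a guide, about 222 before attrition and 222/0.8 = 277.5 → 278 after it, assuming zero correlation; the Hypothesis 4 figure would follow from the rerun.

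The cost is a few restated numbers and, in the last case only, one software run. No additional participants are required.

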Does regular meditation practice after initial instruction increase mental well-being?	The amount of meditation practice during approximately the first year predicts practitioners’ mental well-being, such that a greater amount leads to greater mental well-being.	A number of 242 gives 95% power to detect the variance in mental well-being (SWEMWBS^b^) explained by monthly meditation practice observed in linear mixed model analysis, at a 2-tailed significance level of 0.05, accounting for an estimated 20% loss to follow-up.	Linear mixed model of the fixed effect of the amount of meditation in the past month on mental well-being in the past 2 weeks (SWEMWBS), controlling for the confounding factors of age, caring status, education, mental health diagnosis, commitment to meditation, and membership of a practice support community at baseline.	A positive/negative and statistically significant association between the amount of meditation in the past month on mental well-being in the past 2 weeks will suggest that regular meditation practice after initial instruction increases/decreases mental well-being in a linear fashion. A nonsignificant association will suggest an absence of evidence for this.
Is the effect of continued meditation practice after initial instruction on quality of life moderated by whether a practitioner’s meditation tradition is spiritual or secular?	Whether the meditation tradition is secular or spiritual will moderate any effects on quality of life (nondirectional)	Sampling plan follows hypothesis 1, with an additional 20%, n=627, powered to detect effect of f^2^=0.0318	Linear mixed model of the fixed effect of the amount of meditation in the past month and the interaction effect of tradition spirituality on quality of life in the past week (EQ-HWB-9), controlling for the confounding factors of age, caring status, education, mental health diagnosis, commitment to meditation, and membership of a practice support community at baseline.	A positive/negative statistically significant beta coefficient for this interaction will indicate that regular meditation practice within a spiritual tradition will have a larger/smaller effect on quality of life than practicing within a secular tradition. A nonsignificant association will suggest absence of evidence for this.

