Is the effect of continued meditation practice after initial instruction on mental well-being moderated by whether a practitioner’s meditation tradition is spiritual or secular?	Whether the meditation tradition is secular or spiritual will moderate any effects on mental well-being (Hypothesis 4, nondirectional).	Sampling plan follows hypothesis 2, with an additional 20%, n=291, powered to detect effect of f^2^=0.045	Linear mixed model of the fixed effect of the amount of meditation in the past month and the interaction effect of tradition spirituality on mental well-being in the past 2 weeks (SWEMWBS), controlling for the confounding factors of age, caring status, education, mental health diagnosis, commitment to meditation, and membership of a practice support community at baseline.	A positive/negative statistically significant beta coefficient for this interaction will indicate that regular meditation practice within a spiritual tradition will have a larger/smaller effect on mental well-being than practicing within a secular tradition. A nonsignificant association will suggest absence of evidence for this.
What is the association between the costs and outcomes of meditation practice?	No hypothesis	Our sampling plan will follow hypothesis 1.	We will conduct an exploratory cost-effectiveness analysis to compare effects (quality of life) with a range of costs (costs of mental health support, costs associated with meditation practice)	Results will be presented as an ICER^c^ with associated sensitivity analysis, as outlined above.
What is the incidence and functional impact of meditation-related adverse effects	No hypothesis	—^d^	Proportion and CIs of the frequency, severity of impairment on daily function, and duration of impairment of initial meditation-related challenging experiences and adverse effects (MRAEs)	—

a EQ-HWB-9: 9-item EuroQoL Health and Wellbeing.

b SWEMWBS: Short Warwick-Edinburgh Mental Well-Being Scale.

c ICER: incremental cost-effectiveness ratio.

d Not applicable.

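### Hypothesis 3 has two different detectable moderation effects (f² of 0.0352 and 0.0318) for the same 627 participants, and neither fits the planned one-degree-of-freedom interaction test

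*Protocol article*

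**What the plan says.** Sampling Plan, Hypotheses 3 and 4, calls the likely moderation effects highly uncertain and does not derive a sample size from them. Instead: "we plan to increase our sample by an additional 20% from what is required for power to test our primary outcome (Hypothesis 1) to 627". With that sample, and "setting power to 0.95 and significance to 0.05 2-tailed", it concludes that "we will be powered to detect a moderation effect of f^2^=0.0352".

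Table 1 covers the same hypothesis in its sampling-plan column: "Sampling plan follows hypothesis 1, with an additional 20%, n=627, powered to detect effect of f^2^=0.0318". For Hypothesis 4 the same column reads: "Sampling plan follows hypothesis 2, with an additional 20%, n=291, powered to detect effect of f^2^=0.045".

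The planned test is described in three places. Measures divides participants into two tradition groups. The Sampling Plan for Hypothesis 1 says that practice amount will be continuous in the final analysis. The Analysis Plan adds the tradition variable and its interaction with amount to the Hypothesis 1 model. Table 1 then rests the conclusion on one coefficient: "A positive/negative statistically significant beta coefficient for this interaction will indicate that regular meditation practice within a spiritual tradition" has a larger or smaller effect than secular practice.

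**The concern.** Sample size, power and alpha are the same in the two statements for Hypothesis 3, so the detectable effect should be the same. It differs by about 11% (0.0352 / 0.0318 = 1.107).

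A binary variable times a continuous variable is a single term, so the test has one degree of freedom. Both printed values look too large for a 1-df test at this n. The Hypothesis 4 figure does not.

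At stake is the only quantitative statement of what the study can detect on moderation of quality of life. As printed it contradicts itself, describes a test other than the planned one, and cannot be compared with the figure for Hypothesis 4.

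**Working it through.** **Inputs.** n = 627, power 0.95 and two-tailed alpha 0.05 (Sampling Plan, Hypotheses 3 and 4). Printed f² for Hypothesis 3: 0.0352 (Sampling Plan) and 0.0318 (Table 1). Printed f² for Hypothesis 4: 0.045 at n = 291 (Table 1). Loss to follow-up: 20% (Sampling Plan, Hypothesis 1). The number of tested terms behind each f² is not stated, so it was varied.

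**Sample size.** 435 × 1.2 = 522 and 522 × 1.2 = 626.4, rounded up to 627. For Hypothesis 4, 242 × 1.2 = 290.4, rounded up to 291. Both reproduce.

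**Formula.** For u tested terms in a regression with p predictors, the detectable f² solves P(F′(u, n − p − 1; λ) > F critical at 0.05) = 0.95, with noncentrality λ = f² × n. Changing p between u and 15 does not alter the fourth decimal at n = 627.

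**Results at n = 627, 95% power:**

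| Tested df | Detectable f² |
|---|---|
| 1 | 0.0208 |
| 2 | 0.0248 |
| 3 | 0.0276 |
| 4 | 0.0298 |
| 5 | 0.0318 |
| 6 | 0.0336 |
| 7 | 0.0352 |
| 8 | 0.0367 |
| 9 | 0.0381 |

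So Table 1's 0.0318 is the 5-df value and the Sampling Plan's 0.0352 is the 7-df value, each to four decimals. The planned 1-df test gives 0.0208.

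**Check on the method.** At n = 291, 1 df gives 0.0450, which is the printed Hypothesis 4 figure. The noncentralities show the same split:
- Hypothesis 4: 0.045 × 291 = 13.1
- 1-df value at 627: 0.0208 × 627 = 13.0
- Hypothesis 3, Table 1: 0.0318 × 627 = 19.9
- Hypothesis 3, Sampling Plan: 0.0352 × 627 = 22.1

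**Size of the discrepancy.** 0.0318 / 0.0208 = 1.53 and 0.0352 / 0.0208 = 1.69, so the printed values are 53% and 69% above the 1-df value. Put the other way, a 1-df test at 627 would have 99.4% power at 0.0318 and 99.7% at 0.0352, not 95%. A 1-df test with 95% power would need 411 and 372 participants respectively, and neither number appears in the article.

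**Allowing for loss.** 627 × 0.8 = 501.6, about 502 retained, gives a 1-df f² of 0.0260. Undoing the plan's own multiplication, 627 / 1.2 = 522.5, about 522, gives 0.0250. At the 600 named in the abstract, with no loss, it is 0.0217.

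**The case against.** The strongest reply is that nothing hangs on the figure. The sample was set by a flat 20% increase, not from f². Moderation is not the primary hypothesis. The error also runs in the safe direction: a 1-df test could detect a smaller effect than either figure claims. All of that stands and limits the importance of the point, but it does not make two conflicting values for one quantity correct.

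A second reply is that the formula treats each participant as one observation, whereas the planned test is a mixed model on monthly data. That stands too. No value here, including 0.0208, is the detectable effect of the planned mixed model, and REML also uses data from participants who leave early. Still, the printed figures match this formula at whole-number degrees of freedom, so it is a fair basis for saying that they do not belong to a 1-df test.

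A reader might go further in four ways that the article does not support:
- **That 0.0352 comes from an overall test of the seven Hypothesis 1 predictors** (amount plus six confounders). The count fits, but the moderation model has at least nine terms once tradition and the interaction are added, and 9 df would give 0.0381. Caring status and education may also take several terms each. The cause is not established.
- **That f² will be used to interpret a null result.** Table 1 says only that nonsignificance suggests absence of evidence, and no rule refers to f².
- **That 0.045 for Hypothesis 4 is also wrong.** It is correct for 1 df at the n printed beside it.
- **That the sample is too small for Hypothesis 3.** The recalculation points the other way.

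**Conclusion.** The point holds. That the two Hypothesis 3 figures contradict each other is plain on the page and needs no inference. That neither belongs to the planned single-coefficient test is a back-calculation. It assumes the standard noncentral-F regression formula with λ = f² × n, and is supported by four-decimal matches at 5 and 7 df and by the Hypothesis 4 figure matching at 1 df. Under that formula the 1-df value is 0.0208 at 627, or 0.0250 to 0.0260 with 522 to 502 retained. The last two are equally defensible approximations, not a single right answer.

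This is a wrongly stated power property, conservative in direction, with no effect on sample size, model or test. It should be corrected because it is wrong as printed and very cheap to put right.

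**What to change.** In both Table 1 (Hypothesis 3 row) and the Sampling Plan, replace 0.0318 and 0.0352 with one 1-df figure, and state the tested degrees of freedom and the n beside it. Use about 0.021 if it is quoted at 627 enrolled, or about 0.025 to 0.026 if it is quoted at the 522 to 502 retained after 20% loss. Add that it is a per-participant regression approximation that ignores the repeated measures.

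For Hypothesis 4, keep 0.045 as the value for n = 291. Note that Table 3 schedules the SWEMWBS for the whole cohort, so the 1-df figure given for Hypothesis 3 applies to the actual sample for Hypothesis 4 as well.

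The cost is two numbers and about two sentences. Design, sample size and analysis do not change.
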